### Hypothesis

The CGMS has been shown to potentially improve glycaemic control as defined by HbA1c levels. Since obstetric complications in diabetic pregnancies, especially macrosomia, seem to be related to glycaemic control, we hypothesise that the additional use of CGMS will reduce the macrosomia rate by 30 percent.

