### Intervention

The continuous glucose monitoring system (CGMS) is a new technique that is efficacious in the monitoring of diabetic women. It can provide a comprehensive glucose profile over a 5–7 days period. The CGMS (CGMS Medtronic: Minimed, Northridge,CA) measures glucose levels through electro-chemical detection in the extracellular fluid of the abdominal subcutaneous tissue and stores values in a range of 2.2 - 22.2 mmol/L every 10 sec. An average value is stored in the monitor every 5 minutes, providing up to 288 blood glucose measurements (12x24) a day. The subjects are unaware of the results of the sensor measurements during monitoring and need to continue self-monitoring of blood glucose while carrying the monitor. After 5–7 days glucose profiles are obtained from the monitor and can be evaluated by the diabetologist and dietary or insulin therapy changes can be advised.

All study participants will determine their glycaemic control by self-monitoring of blood glucose levels (4–8 times/day) and HbA1c-levels (every 4 weeks) throughout the course of pregnancy. Figure 1 represents a flowchart of the study.

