### Statistics

#### Sample size

We anticipate that a reduction of macrosomia from 45% to 30% will outweigh the costs of the additional use of the CGMS. As we assume 10% protocol violations and drop out, we need to randomise 300 women (Alpha-error .05, Beta-error .20, one-sided test) of which 150 will receive additional CGMS use and 150 will be controls.

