#### Data analysis

Data will initially be analysed according to the intention to treat method. The main outcome variable, macrosomia, will be assessed by calculating rates in the two groups, relative risks and 95% confidence intervals as well as numbers needed to treat. The secondary outcome measures will be addressed in a similar manner. Continuous outcome measures will be compared using parametric and non-parametric tests, depending on the distribution of the data. We plan a subgroup analysis of women with diabetes type 1 and type 2 diabetes and gestational diabetes.

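### The crude relative risk for macrosomia is valid but uses no baseline information; adjusting for diabetes type and, where recorded before allocation, HbA1c is an optional, cheap gain in precision that may be close to nil

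*Protocol article*

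**What the plan says.** Under Data analysis, the primary outcome is to be "assessed by calculating rates in the two groups, relative risks and 95% confidence intervals", together with numbers needed to treat. No covariate or stratum is named for this comparison. Diabetes type is the stratification factor under Recruitment and randomisation, but in the analysis it returns only as a planned subgroup analysis.

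The Hypothesis section describes glycaemic control in terms of HbA1c and then says that "obstetric complications in diabetic pregnancies, especially macrosomia, seem to be related to glycaemic control". It gives no strength for that relation. The Intervention section has all participants measure "HbA1c-levels (every 4 weeks) throughout the course of pregnancy". No section specifies an HbA1c value taken before randomisation. Outcome measures lists HbA1c during pregnancy as a secondary maternal endpoint.

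The Sample size section uses rates of 45% and 30%, with "Alpha-error .05, Beta-error .20, one-sided test", allows for "10% protocol violations and drop out", and concludes that "we need to randomise 300 women".

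**The concern.** A logistic model with prognostic baseline variables, averaged back to a marginal relative risk, targets the same quantity as the crude ratio. It usually has a smaller standard error when the covariates predict the outcome. The trial's rationale runs through glycaemic control, so HbA1c at entry is a natural candidate. Women of the same diabetes type still differ in entry HbA1c, so adjusting for type alone would not capture that variation.

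What is at stake is the width of one confidence interval, the one on the primary outcome. It is worth settling in advance, because in an open trial an adjustment chosen after the data are seen is easily disputed.

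**Working it through.** **1. The plan's own figure.** Inputs from Sample size: 45% v 30%, one-sided alpha 0.05, power 80%, 10% loss. With pooled variance and mean rate 0.375:

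n per arm = [1.645·√(2·0.375·0.625) + 0.842·√(0.45·0.55 + 0.30·0.70)]² / 0.15² = 127.8, so 128.

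Dividing by 0.9 gives 143 per arm, 286 in all. With a continuity correction it is 141 per arm, then 157, or 314 in all. The stated 300 lies between the two. At 300 less 10%, or 135 per arm, one-sided power is 81.9%. The stated size is therefore adequate, on its own terms, for an unadjusted comparison.

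**2. Precision of the crude estimate at 135 per arm.**

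SE(log RR) = √[0.55/(0.45·135) + 0.70/(0.30·135)] = √0.02634 = 0.162.

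With RR = 0.30/0.45 = 0.667, the 95% CI is exp(−0.405 ± 1.96·0.162) = 0.485 to 0.916.

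**3. What a covariate could add.** If it explains a share R² of the outcome variance, the SE is multiplied by roughly √(1 − R²). The documents give no R², so 0 to 0.15 is assumed.

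| Assumed R² | CI narrower by (log scale) | 95% CI at RR 0.667 | One-sided power |
|---|---|---|---|
| 0 | 0% | 0.485–0.916 | 81.9% |
| 0.02 | 1.0% | 0.487–0.913 | 82.6% |
| 0.05 | 2.5% | 0.489–0.909 | 83.6% |
| 0.10 | 5.1% | 0.493–0.901 | 85.3% |
| 0.15 | 7.8% | 0.497–0.894 | 87.1% |

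At R² 0.10 the gain is worth 270/0.9 = 300 evaluable women in place of 270.

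**4. Simulation against the crude estimate.** 6,000 trials per setting, 135 per arm, one standardised baseline covariate, logistic model standardised to a marginal RR. The ratio of adjusted to crude SE was 1.002, 0.994, 0.990, 0.951 and 0.923 at assumed odds ratios per SD of 1.0, 1.3, 1.5, 2.0 and 2.5. The mean RR was 0.66 to 0.67 with and without adjustment.

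**5. Simulation beyond diabetes type.** 4,000 trials per setting, 45% v 30%, three equal type strata (assumed). A model with arm and type was compared with the same model plus baseline HbA1c.

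| Assumed odds ratio per SD within type | Variance ratio, without/with HbA1c | Variance reduction | Equivalent extra women at N = 270 |
|---|---|---|---|
| 1.25 | 1.011 | 1 − 1/1.011 = 1.1% | 0.011·270 ≈ 3 |
| 1.5 | 1.035 | 1 − 1/1.035 = 3.4% | 0.035·270 ≈ 9 |
| 2.0 | 1.097 | 1 − 1/1.097 = 8.8% | 0.097·270 ≈ 26 |

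The two simulations agree: little gain at an odds ratio of 1.5 or less, and a variance reduction of about 9 to 10% at 2.0 (in step 4, 1 − 0.951² = 9.6%).

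**6. Chance imbalance.** With 150 per arm, the SE of the difference in mean standardised HbA1c is √(2/150) = 0.115, so a two-SE imbalance is 0.23 SD. On a linear approximation, the crude risk difference would move by 0.375·0.625·ln(1.5)·0.23 = 2.2 points at an odds ratio of 1.5, or 0.375·0.625·ln(2)·0.23 = 3.7 points at 2.0, against a target of 15. This is the same variation that steps 3 to 5 measure, seen in a single trial; it is not an additional effect.

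**The case against.** **The crude analysis is not wrong.** Under 1:1 randomisation it is valid, the sample size was built for it, and a full protocol or analysis plan that is not shown may add an adjusted estimate. All of this stands. What remains is that the article positively states a primary method, and that method can be improved at little cost.

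**A reader might infer that the plan names HbA1c as a driver of macrosomia and already holds a baseline value.** The documents support neither. The Hypothesis section says only that the two seem related. The article's background cohort had a mean HbA1c of 44 mmol/mol, described as acceptable control, and still had 45% macrosomia. That does not disprove an association, but it gives no ground for assuming a strong one. A four-weekly schedule during pregnancy makes a value near entry likely but does not establish one before allocation.

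**A reader might infer that an imbalance in entry HbA1c would bias the crude relative risk.** It would not. Such an imbalance is sampling variation that the unadjusted interval already covers.

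**A reader might infer that the trial is short of power and that adjustment would repair it.** On the stated one-sided basis, power is about 82% at 135 per arm against a planned 80%. Against a two-sided 95% interval it is about 72%, but the mismatch between a one-sided design and a two-sided interval is a separate matter. Adjustment would not close it: in the simulation with type strata, two-sided power rose from 71.2% to 74.7% at an odds ratio of 2.0.

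**Entry HbA1c is taken at different gestations:** before 16 weeks in pre-existing diabetes and up to 30 weeks in gestational diabetes (Participants). This stands, and is why HbA1c should enter only together with type and centred within it. A single slope across types remains a working assumption.

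**Conclusion.** The point holds as a small, conditional gain in efficiency, of optional severity. The primary comparison uses no baseline information. Diabetes type is the better documented omission because it is the stratification factor; HbA1c may add to it if a value from before allocation is recorded.

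Beyond type, the variance of the log relative risk would fall by about 1%, 3% and 9% at odds ratios per SD of 1.25, 1.5 and 2.0. The odds ratios and the equal type strata are assumptions, and the documents contain nothing to choose among them, so the gain may be close to nil. The risk in the other direction is negligible: with a covariate that predicts nothing, the simulated SE ratio was 1.002.

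**What to change.** Make the primary estimate a marginal (standardised) relative risk and risk difference from a logistic model with arm, diabetes type and, where recorded at or before randomisation, HbA1c as a linear term centred within type. Give robust or bootstrap 95% confidence intervals, and show the crude rates and crude relative risk beside it. If a few baseline values are missing, fill them with the type-specific mean. If no HbA1c from before allocation is available, adjust for type alone.

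State that HbA1c measured after randomisation is never a covariate: it is a secondary outcome, and CGMS use may change it.

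Cost: a sentence or two in the analysis section and a few lines of code, with no additional women. The estimate is slightly less transparent than two raw rates, and each baseline value must be dated before allocation.

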### Participants

Pregnant women with pre-existing diabetes mellitus (type 1 or 2) before gestational age of 16 weeks or with gestational diabetes requiring insulin therapy before 30 weeks gestational age will be asked to participate. Inclusion criteria include maternal age of at least 18 years and need for insulin treatment by means of injections or insulin pump. Patients with severe medical or psychological comorbidity will be excluded. Multiple pregnancies will also be excluded since they require different standards of obstetric evaluation.

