### Recruitment and randomisation

Potential study candidates will be identified by their gynaecologist or internist. Patients eligible for participation in the study will be invited for additional counselling by a research nurse, to ensure that they will be fully informed on the nature of the study by means of both oral and written information. Patients who agree to participate will be asked to sign a written informed consent of which they will receive a copy.

After providing informed consent for the participation in the study, the patient will be randomly allocated to either standard care or standard care and additional CGMS use. Randomisation will be done on a 1:1 basis over the internet, stratified for type of diabetes, using a web-based program. The current inclusion status is being displayed on the GlucoMOMS trial website http://www.studies-obsgyn.nl/glucomoms/page.asp?page_id=1027

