### Outcome measures

#### Main study parameter/endpoint

Outcome measures of the trial are related to obstetric complications and glycaemic control. Macrosomia is the most frequent complication of diabetes during pregnancy and is associated with neonatal morbidity and long term effects. Therefore, the primary outcome measure is macrosomia rate. Macrosomia is defined as a birth weight above the 90^th^ centile.

Secondary maternal endpoints are: pre-eclampsia (defined as systolic blood pressure ≥ 140 mmHg or diastolic blood pressure ≥ 90 mmHg occurring after 20 weeks of gestation and simultaneous proteinuria of ≥300 mg/24 hours) caesarean section, hypoglycemia (subdivided as biochemical hypoglycemia (self-measured blood glucose < 3.9 mmol/l) or symptomatic hypoglycemia (symptoms of hypoglycemia confirmed by self-measured blood glucose < 3.9 mmol/l) or severe hypoglycemia, (prompting the need for help by another person)), HbA1c levels throughout the course of pregnancy, glucose variability (Mean Absolute Glucose change per patient per hour) and relative glucose variability (Coefficient of Variability) [18].

Secondary neonatal endpoints are: birth weight, preterm birth, perinatal death, birth trauma (including shoulderdystocia, clavicle fracture or Erb’s palsy), neonatal hypoglycemia (defined as blood glucose < 2.6 mmol/l), respiratory distress syndrome (RDS), broncho pulmonal dysplasia (BPD), intraventricular haemorrhage II B or worse, necrotizing enterocolitis (NEC), and sepsis.

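### HbA1c and other continuous secondary outcomes are to be compared by a test chosen from the observed distribution, which leaves the effect measure open and makes no stated use of baseline, repeated values or the stratification factor

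*Protocol article*

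**What the plan says.** The Data analysis section gives one rule for all continuous outcomes: "Continuous outcome measures will be compared using parametric and non-parametric tests, depending on the distribution of the data". It names no covariate and no longitudinal model.

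The outcomes under that rule include birth weight, the two glucose-variability measures and HbA1c. The Intervention section schedules "HbA1c-levels (every 4 weeks) throughout the course of pregnancy" for all participants, and the Outcome measures section lists the endpoint as "HbA1c levels throughout the course of pregnancy", without a time point or summary. Birth weight stands beside delivery timing in the list: "Secondary neonatal endpoints are: birth weight, preterm birth, perinatal death".

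Under Recruitment and randomisation: "Randomisation will be done on a 1:1 basis over the internet, stratified for type of diabetes, using a web-based program". In the Data analysis section, diabetes type reappears only here: "We plan a subgroup analysis of women with diabetes type 1 and type 2 diabetes and gestational diabetes". The Participants section admits women with pre-existing diabetes "before gestational age of 16 weeks or with gestational diabetes requiring insulin therapy before 30 weeks gestational age", so women will contribute HbA1c series of different lengths.

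**The concern.** The rule suits an outcome measured once. HbA1c is a series. To apply the rule, someone must first pick a visit, average the visits or test each one, and the article does not fix which. The trial is open-label, so it is better to settle this beforehand. HbA1c also matters to the argument of the trial: the Hypothesis section has CGMS act on macrosomia through glycaemic control.

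Two features of the rule go beyond brevity.

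- The choice of test depends on the data. A parametric test addresses a difference in means; a rank test addresses whether values in one arm tend to exceed those in the other. The quantity reported would be settled only after the distribution is seen.
- Diabetes type is built into the allocation but has no stated role in the main comparison. Baseline HbA1c, usually the strongest predictor of later HbA1c, has no stated role either.

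At stake is the precision and clarity of secondary results, not the validity of the randomised comparison.

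**Working it through.** **Inputs.** The article states no precision or sample-size figure for HbA1c or birth weight, so there is none to reproduce. The Sample size section gives 300 women and 10% protocol violations and drop-out: 300 × 0.90 = 270, or 135 per arm. The correlation r between baseline and follow-up HbA1c, the share of variance explained by diabetes type, and all birth-weight parameters are assumptions. Tests below are two-sided at 5%.

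**1. Baseline adjustment, one follow-up value.** Variance factor = 1 − r². Standard error (SE) factor = √(1 − r²). Effective sample gain = 1/(1 − r²). Without adjustment, the effect detectable with 80% power is (1.960 + 0.842) × √(2/135) = 0.34 SD. The last column is the power for that same effect after adjustment.

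| r (assumed) | Variance factor | SE factor | Sample gain | Power at 0.34 SD |
|---|---|---|---|---|
| 0.3 | 0.91 | 0.954 | 1.10 | 84% |
| 0.5 | 0.75 | 0.866 | 1.33 | 90% |
| 0.7 | 0.51 | 0.714 | 1.96 | 97.5% |

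**2. Repeated values.** Assume equal correlation r between all values and a constant treatment effect. The mean of k follow-up values, adjusted for baseline, has variance (1 + (k − 1)r)/k − r², relative to one unadjusted follow-up value. For k = 3:

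- r = 0.5: 0.667 − 0.25 = 0.42
- r = 0.7: 0.80 − 0.49 = 0.31

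This further gain belongs to an effect averaged over visits. A contrast at one point in late pregnancy gains mainly what step 1 shows.

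**3. Stratification factor.** If diabetes type explains a share R² of the variance, adjustment multiplies the SE by √(1 − R²). The real size of an unadjusted 5% test after stratified allocation is 2 × (1 − Φ(1.96/√(1 − R²))).

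- R² = 0.05: SE factor 0.975, real size 0.044
- R² = 0.30: SE factor 0.837, real size 0.019

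Omitting type makes the test conservative, not biased. The gains in steps 1 and 3 overlap, since baseline HbA1c may differ by type, and should not be multiplied.

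**4. Birth weight and delivery timing.** Simulation: 4,000 runs, 135 per arm, 180 g per week of gestation, SD of gestational age 1.5 weeks, residual SD 450 g, direct effect −150 g. All values are illustrative.

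| Scenario | True total effect | Unadjusted estimate | Adjusted for gestational age |
|---|---|---|---|
| No shift in delivery | −150 g | −148 g (SE 64.5) | −149 g (SE 55.6) |
| Delivery 0.5 week later with CGMS | −150 + 180 × 0.5 = −60 g | −61 g | −152 g |
| Same shift, with a shared cause of timing and weight | −60 g | −59 g | −119 g |

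The unadjusted comparison recovers the total effect each time. When delivery shifts, adjustment answers a different question; with a shared cause it gives neither the total nor the direct effect.

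**The case against.** The strongest objection is that most of this is detail a condensed article leaves to a fuller protocol or analysis plan, neither of which is shown. That stands for silence on covariates and models, and absence alone would not support the point. It does not dispose of the sentence that is there: a rule is stated for every continuous outcome, it depends on the data, and it fits a repeated measure poorly.

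A reader might infer several stronger things that the article does not support.

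- *That unadjusted visit-by-visit tests are planned.* The text says neither unadjusted nor visit-by-visit.
- *That delivery timing biases the birth-weight comparison.* Gestational age at delivery arises after randomisation and may be affected by CGMS. The comparison in grams is valid for the total effect (step 4), and preterm birth is reported as its own endpoint.
- *That early HbA1c values come only from women with pre-existing diabetes.* The Participants section sets an upper limit for gestational diabetes but no lower one. Any change in case mix over gestation affects both arms of a stratified 1:1 trial.
- *That diabetes type is ignored.* It stratifies the allocation and defines a planned subgroup analysis. Only a role in the main comparison is not stated.

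It is also fair to object that the gain rests on correlations from outside the documents. At r = 0.3 it is only 1.10.

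**Conclusion.** The point holds as a minor one. The stated rule leaves the HbA1c effect measure open until the data are seen and makes no stated use of information the design provides. Under assumed correlations of 0.3 to 0.7, baseline adjustment alone would be worth an effective sample gain of 1.10 to 1.96. Adjustment for diabetes type would cut the SE by about 3% to 16% if type explains 5% to 30% of the variance. These ranges are assumptions; the documents neither support nor exclude any value within them.

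The loss is one of precision and clarity on secondary outcomes. No bias in HbA1c or birth weight follows from the stated method, and the macrosomia analysis and its sample size are unaffected.

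**What to change.** Replace the sentence on continuous outcomes with the following.

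- **HbA1c:** a linear mixed model on the 4-weekly values, with treatment, gestational age and their interaction, adjusted for baseline HbA1c and diabetes type, and one prespecified treatment contrast in late pregnancy. Define baseline as the first, pre-allocation value; the article does not define one.
- **Birth weight:** in grams, by a linear model adjusted for diabetes type. Do not add gestational age at delivery as a covariate. Add a gestational-age-standardised z-score as a supplementary outcome only.
- **Skewed outcomes:** a transformation named in advance, such as the logarithm, in place of a switch between tests.

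The cost is a change of wording and slightly more analysis work, with no extra women or visits. One thing to confirm first: the article does not name the reference behind the 90th centile and does not mention infant sex, so the data needed for the z-score cannot be assumed to be collected. If this is already settled in a full analysis plan, a sentence in agreement with it is enough.

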#### Interim analysis

An interim analysis will be performed after the inclusion of 150 women. This analysis will be done by an independent data and safety monitoring committee, which will not be aware of the allocation of sensor or routine control when they judge data on effectiveness. In case of strong effects, the safety monitoring committee can advise to stop the study. Furthermore, each SAE will be reported to the data and safety monitoring committee.

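### The effectiveness interim is triggered by 150 inclusions although macrosomia is known only at birth, and the committee's masking does not fit the one-sided benefit hypothesis

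*Protocol article*

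**What the plan says.** Four parts of the protocol article bear on this point.

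- **Interim analysis.** The trigger is a count of women enrolled: "An interim analysis will be performed after the inclusion of 150 women". An independent committee assesses the data, "which will not be aware of the allocation of sensor or routine control when they judge data on effectiveness". The stopping rule is "In case of strong effects, the safety monitoring committee can advise to stop the study". Serious adverse events also go to the committee one by one.
- **Outcome measures.** The primary outcome is macrosomia, a birth weight above the 90th centile, so it does not exist before delivery.
- **Participants.** Entry is early: "Pregnant women with pre-existing diabetes mellitus (type 1 or 2) before gestational age of 16 weeks", or gestational diabetes needing insulin before 30 weeks.
- **Sample size.** The design is directional: "We anticipate that a reduction of macrosomia from 45% to 30% will outweigh the costs of the additional use of the CGMS", and "we need to randomise 300 women (Alpha-error .05, Beta-error .20, one-sided test". No share of the 5% is visibly set aside for the interim, and Data analysis plans ordinary 95% confidence intervals.

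**The concern.** The trigger counts women at entry, but the outcome arrives months later. When the 150th woman is included, those enrolled recently can contribute a birth weight only if they delivered early. The available outcomes therefore over-represent late-entry gestational diabetes and preterm births. A look planned at half the trial would be made on much less.

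The masking raises a separate problem. A one-sided test asks whether CGM is better, and a committee that does not know which arm is CGM cannot apply that question. The article's own Background shows that the opposite direction is not fanciful. One cited trial found macrosomia in 43% with CGM and 30% in controls, and another is said to hint at an adverse effect through small-for-gestational-age infants. With coded arms, 43% against 30% (13 points) looks much like the planned 45% against 30% (15 points).

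At stake is whether advice to stop would rest on enough outcomes, and on a known direction of effect.

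**Working it through.** **1. The plan's own figure.** With 45% v 30%, one-sided 5%, 80% power and the pooled-variance formula, the mean rate is 0.375:

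n per arm = [1.645·√(2·0.375·0.625) + 0.842·√(0.45·0.55 + 0.30·0.70)]² / 0.15² ≈ 128.

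For the stated 10% loss ("As we assume 10% protocol violations and drop out"), 128/0.9 gives 143 per arm, 286 in total. The planned 300 is consistent with rounding up: 135 evaluable women per arm (150 × 0.9) give 81.9% power. The sample size is not in question. It sets the 300 used as full information below.

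**2. Births available at the 150th inclusion.** Accrual rate, case mix and exact entry weeks are not in the article. The assumptions are:

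- 300 women over 18 to 36 months, that is 300/18 = 16.7 to 300/36 = 8.3 per month;
- 50 to 80% with pre-existing diabetes;
- 26 weeks from entry to birth in pre-existing diabetes and 10 weeks in gestational diabetes.

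Under steady accrual, undelivered women = monthly rate × (share × 26 + (1 − share) × 10) / 4.345.

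| Accrual | Pre-existing | Mean wait | Undelivered | Births of 150 |
|---|---|---|---|---|
| 18 months | 80% | 22.8 wk | 87 | 63 |
| 18 months | 50% | 18.0 wk | 69 | 81 |
| 36 months | 80% | 22.8 wk | 44 | 106 |
| 36 months | 50% | 18.0 wk | 35 | 115 |

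As a fraction of 300, this is 63/300 = 21% to 115/300 = 38%, against 150/300 = 50% if all had delivered.

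As a check, take the shortest waits compatible with birth at 37 weeks, with entry right at the limits (21 and 7 weeks). In the most favourable row the mean wait is 14 weeks, and 8.33 × 14/4.345 ≈ 27 women would still be undelivered, leaving 123 births.

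**3. What the lost information costs.** For 45% v 30%, a look at nominal one-sided 5% has power 60% with 75 births per arm, 52% with 60, 43% with 45 and 38% with 37. A stricter boundary would have less.

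**4. Type I error, by boundary.** With two looks, the test statistics are bivariate normal with correlation √t, where t is the information fraction. Overall error = 1 − P(Z₁ < c₁, Z₂ < c₂), with c₂ = 1.645.

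| t | Interim also at one-sided 5% | Interim at one-sided p<0.001 |
|---|---|---|
| 0.5 | 8.0% | 5.02% |
| 0.4 | 8.3% | 5.03% |
| 0.3 | 8.6% | 5.04% |
| 0.2 | 8.9% | 5.06% |

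**5. Masking against direction.** No arithmetic applies. Sample size states a one-sided hypothesis, while Interim analysis withholds arm identity from those judging effectiveness. A rule for benefit needs the sign of the difference, and coded arms give only its absolute size.

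**The case against.** Several stronger readings are tempting, and the article does not support them.

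- **That the interim lacks an error-controlled boundary.** The article states none, but a boundary commonly sits in the full protocol, analysis plan or committee charter. The 8.0 to 8.9% applies only if nominal one-sided 5% is used at both looks, and the advisory wording about strong effects suggests something stricter. If the planned two-sided 95% intervals were the criterion at both looks, the total error of 8.3% (t = 0.5) to 9.1% (t = 0.25) would halve to about 4.2 to 4.5% in the benefit direction, below the 5% of the sample size.
- **That the committee cannot see which arm does better.** Only the identity of the arms is withheld; nothing says the data are pooled. Coded results would show that one arm does better, but not whether it is CGM.
- **That the early subset biases the comparison.** Randomisation is 1:1 and stratified by type of diabetes. The loss is in information and representativeness.
- **That the trial could run on through harm.** The masking covers effectiveness data, and serious adverse events are reported to the committee separately. A strong harmful difference could also prompt advice to stop.

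Other points deserve weight. The trigger may be meant as the outcomes of the first 150 women. Masked-label review is accepted practice. The 43% v 30% result was not significant (p = 0.09) and came from a real-time device, whereas this trial's readings are hidden from the women during monitoring and reviewed afterwards.

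Two things stand. The text counts inclusions and does not mention births. A directional hypothesis cannot be judged by people who do not know the direction.

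**Conclusion.** The point holds as a matter of protocol wording in two places.

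The trigger, taken literally, comes too early for the outcome. The shortfall is about 35 to 87 of 150 birth weights. Its size rests on assumed accrual, case mix and time to birth, but its existence follows from the entry criteria and the nature of the outcome.

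The masking conflicts with the one-sided design: the same strong effect on macrosomia could be benefit or harm, and the committee could not say which. This does not depend on the assumptions.

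The missing boundary is a conditional point only. Inflation ranges from almost none to about 8.9%, depending on a rule that may be written down elsewhere. It is worth correcting, at moderate priority, and does not undermine the final analysis by itself.

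**What to change.** - **Trigger.** Define the interim as the analysis of the first 150 randomised women once all have delivered.
- **Committee.** Have an independent statistician supply results by arm, with arm identity available to the committee, and say that the sponsor and investigators do not see them.
- **Boundary.** Refer to where the criterion for strong effects is set. If it is set nowhere, use a Haybittle-Peto rule of one-sided p<0.001 at the interim. The final level can stay at 5%, with overall error about 5.0%.

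The cost on paper is a few sentences in the protocol or charter, with no change to the sample size. The practical cost is delay. The last of the 150 may need 26 weeks to deliver, which is 26/4.345 ≈ 6 months. At 8.3 to 16.7 women per month, 50 to 100 more would enrol, so roughly 200 to 250 of the 300 would be in the trial by then. Early stopping would spare fewer women, and with fast accrual only about 50 would remain to be recruited. The sponsor should weigh that when confirming that the look is still wanted.
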